# A. FORMAL

## Project Name

Influence of wearing a facemask on gait adaptability in people with a neurological disorder.

## Type and number of test centers

The planned study project will be conducted as a monocentric study.

There is only a professional cooperation as described above (2.3.) with [name] and PD [name].

## Cost unit

The study is financed from own funds of the NRZ "Godeshöhe".

In addition, an application for third-party funding was submitted to the Förderverein NRZ Bonn e.V., c/o NRZ Godeshöhe e.V., [name], [name], on May 30, 2021 (decision pending).

## Decision of the ethics committees in the same matter

No application has been made to any other ethics committee.

# B DESCRIPTION OF THE STUDY

## Scientific description of the project

### 1.1 State of research and scientific background

Since the beginning of 2020, the Covid-19 pandemic has repeatedly presented the world with new challenges (WHO, 2021; German government, 2020a; 2021). In particular, the containment of infection rates and the prevention of an overload of the health care system are the focus of all efforts (Bundesregierung, 2020a; 2020c). The measures taken to this end, which are constantly being adapted, affect the daily lives of many people (Bundesregierung, 2020a; 2020b; 2020c; 2020d; 2020e, 2020f; 2020g; 2020h; 2021d). Despite optimistic vaccination progress, the end of the pandemic as well as virus prevention measures is currently not foreseeable (UN, 2021; Freund, 2021; Callisaya et al., 2020). Repeatedly, new waves of infection occur (Bundesregierung, 2020h; 2021a; 2021d RKI, 2021), and with it, more stringent prevention measures (Bundesregierung, 2020i; 2021d).

In particular, the "distance hygiene everyday mask" rules (Bundesregierung, 2020d; 2020e; 2020f; WHO, 2020) and regular ventilation of enclosed spaces (Bundesregierung, 2020g) have proven to be an effective, individual contribution to containing the incidence of infection. The recommendation or regulation to wear everyday masks has now been replaced in many places by the obligation to wear a surgical or FFP2 mask (Bundesregierung, 2020d; 2020j; 2021a; 2021b; 2021c).

All masks, whether medical or non-medical, cover a significant portion of the face. Due to their shape, they definitely protrude into the lower visual field (Kal et al., 2020a, Klatt et al., 2021). It is conceivable that this visual field impairment has an impact on the perception of visual stimuli (Buckley et al., 2011; Rietdyk & Rhea, 2011), because this area of the lower visual field provides important information for any necessary gait adjustments (e.g., avoiding or stepping over obstacles) and safe walking (Buckley et al., 2011). Limitation in this area due to wearing a facemask could contribute to impaired gait performance and safety and possibly increased risk of trips and falls (Klatt et al., 2021; Callisaya et al., 2020; Rietdyk & Rhea, 2011; Lord et al., 2002). Kal and colleagues suggest that this may have an impact on gait safety in the elderly (Kal et al, 2020a). This assumption is supported by the study of Lord and colleagues (2002) in which they could show that already wearing multifocal glasses reduced gait safety. Older people, from the age of 65 years upwards, have an increased risk of falling (Rapp et al., 2014), so it is very likely that further restrictions, such as wearing a facemask, additionally increase the risk of falling. These negative consequences may be even more severe for the population of neurologically predisposed individuals (Klatt et al., 2021; Callisaya et al., 2020), who already have many times the increased risk of falls compared to the average population even without facemask (Beghi et al., 2018).

In people with an underlying neurological disorder, balance, walking, and reaction, among other abilities, are already impaired by the neurological disorders, so that the additional limitations of the visual field and the associated reduced sensory information may not be as easily compensated for by wearing a facemask, and thus the risk of tripping and falling could increase massively (Klatt et al., 2021; Kal et al., 2020a; Yakubovich et al., 2020; Callisaya et al., 2020).

An initial scientific debate has arisen about what affected people could be advised to do to compensate for a supposedly increased risk of falling. Kal et al. (2020a; 2020b) suggest a reduced walking pace for this purpose. They point out that the intuitive and sometimes advised downward gaze may have an additional negative impact on gait safety (Kal et al., 2020a). Callisaya et al, 2020 argue that a slowed walking pace could also reduce gait safety. [name] (2020) points out that various aspects of postural control and mechanical stability are important and argues that reducing walking pace may be appropriate. He adds that this might even prevent falling forward ([name], 2020). Overall, it is clear from the discussion that explicit and personalized recommendations are currently difficult. There is also a lack of actual practical studies that would reveal prevalence and possibly initial limitations and from which initial recommendations could be derived. Therefore, the proposed study aims to investigate these aspects in a neurological cohort. Callisaya et al. (2020) also point out in their paper that education of potentially affected populations is an essential step. The research group states that knowledge of potential risk situations is an important prevention aspect. However, for such educational approaches, it is relevant to know who is actually among those affected. For this purpose, it is essential not only to discuss this question theoretically, but to survey actual prevalence, for example in the neurological population. For this, rather theory-guided scientific discussion leaves open the question of how prevalent the presumed phenomenon actually is in a cohort of neurologically ill people. Therefore, the planned study project will investigate whether "wearing a facemask" versus "not wearing a facemask" has an impact on gait and gait safety.

### 1.2 Study Objective:

In order to verify this, a standardized test to measure the adaptability of gait (CGait) on a VR-based treadmill (C-Mill+VR by Motek) once with and once without a mask as well as specific clinical tests (10 meter walk test, 10mWT; Timed Up and Go Test, TUG, TUG with dual task (TUG+DT) and climbing up and down stairs) will be performed in 50 people with a neurological disease. In addition, the participants will be asked to comment subjectively on their experience of walking with and without a mask using standardized questions.

This study can add clinical data for people with a neurological disease to the existing theoretical scientific discourse and thus make an important contribution to an existing scientific debate. In addition, these findings would serve the affected individuals in that it would allow for a scientifically based recognition of their additional limitations. In addition, following the demands of Callisaya and colleagues (2020) and Kal and colleagues (2020b), this could provide the basis for further clinical investigations regarding possible compensations or recommendations for affected individuals.

### 1.3 Questions and hypotheses:

The main question to be addressed in the planned study is whether wearing the facemask (FFP-2 mask) has an impact on the adaptability of gait (measured by the performance score (%) per CGait subtest for each of the two difficulty levels) in people with a neurological disease (*Question 1*). It is hypothesized that people with a neurological condition (Multiple Sclerosis or Parkinson's disease) will perform significantly worse on individual or all CGait subtests if they wear a facemask than if they do not (*Hypothesis 1*).

However, since clinically observed improvement cannot only be about standardized, objective measurements, the self-assessment of patients must also be given high priority. It should be clarified whether wearing a facemask has an influence on the subjectively perceived walking ability of patients (*question 2*), since it can be assumed that people with a neurological disease notice an impairment of their walking ability by wearing a facemask (*hypothesis 2*). Furthermore, it is known that the subjective perception of the patients might have an influence on gait performance (Hoogkamer et al., 2015; Rosengren et al., 1998), therefore it is relevant to ask about this.

In addition to these two main aspects of the studies, it will also be exploratively investigated whether there is also an influence of wearing a facemask in these clinical tests as well as in walking up and down stairs (*question 3*). It is possible that people with a neurological disorder also show abnormalities in common clinical tests measuring walking ability (stair test, TUG, TUG+DT, 10mWT) (*hypothesis 3*). This finding, albeit exploratory, would provide relevant information for routine clinical testing for all clinicians* who do not have CMill+VR available.

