#### 2.2.1 Primary endpoint

The central parameter of the study is the performance (performance value in %) per CGait subtest in the two difficulty levels of the CGait (if possible for the patients).

The CGait test measures gait adaptability using six different subtests on the CMill + VR treadmill. A comprehensive description of the CGait is provided in the publication by Timmermans et al. (2019).

During the test, the subjects are safeguarded by a harness and the comfortable walking speed is determined at the beginning of the test. This speed is maintained throughout all tasks. In the planned study project, it will also be maintained for the test with and without mask. All tasks of the CGait will be completed by the subjects first with an easy and then with a hard level of difficulty. The subjects are instructed both via an integrated screen and by the therapists.

The performance for the six test tasks (Fig. 2) "goal-directed stepping", "tandem walking", "obstacle avoidance", "slalom walking", "speed adaptations", is measured. It is determined by the proportion of steps where the center of pressure was within the projected area during the mid-stance phase (± half of the foot size for goal-directed stepping and obstacle avoidance). In the "walking with suddenly shifting obstacles and targets" task, the weighted average of correct steps and correctly avoided obstacles is calculated. For each of the six tasks a performance value between 0 and 100% is obtained.

Figure 2: Six subtests of the CGait test from Timmermans et al., 2019.

The performance values of each subtest are compared per condition (1: with facemask, 2: without facemask) and for each difficulty level (easy, hard).

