### 2.5 Statistical evaluation

The collected, pseudonymized data is recorded digitally (dual control principle).

Data analysis is performed using common analysis software IBM SPSS Statistics 27.0 (Armonk, NY) and open source software R (R Foundation for Statistical Computing, Vienna).

At the beginning of the analysis, the data are checked with regard to the fulfillment of required prerequisites. The typical statistical procedures are used for the verification.

Frequencies, medians (with minimum and maximum), or means (with standard deviation) are reported to describe the sample, as appropriate.

To answer research *question 1*, whether wearing the facemask (FFP-2 mask) has an effect on the adaptability of gait (measured with the performance scores of the CGait subtests in both difficulty levels) in people with a neurological disorder, a parametric or non-parametric within-group comparison is calculated, as appropriate.

The *2nd study question*, whether wearing a facemask has an influence on the subjectively perceived walking ability of the patients, is presented using descriptive statistics (frequency tables).

In addition to these two central study questions, research *question 3* of the study, whether there is also an influence by wearing a facemask in the clinical tests measuring walking ability (10mWT, TUG, TUG+DT, and stair test), will be explored. For this purpose, parametric or non-parametric within-group comparisons will be calculated for each subtest, as appropriate.

For all within-group comparisons, the significance level is set at *p* ≤ 0.05.

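### Twelve primary CGait comparisons, each at p ≤ 0.05 with no multiplicity control, leave the false-positive rate for Hypothesis 1 well above 5% unless the outcomes are very highly correlated

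*Protocol*

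**What the plan says.** - Protocol, section 2.2.1, defines the primary endpoint: "The central parameter of the study is the performance (performance value in %) per CGait subtest in the two difficulty levels of the CGait". It adds: "For each of the six tasks a performance value between 0 and 100% is obtained". The comparison is then set out: "The performance values of each subtest are compared per condition (1: with facemask, 2: without facemask) and for each difficulty level (easy, hard". No composite score, lead subtest or testing order is named.
- Protocol, section 1.3, words Hypothesis 1 as the expectation that patients "will perform significantly worse on individual or all CGait subtests if they wear a facemask than if they do not".
- Protocol, section 2.5, says that for question 1 "a parametric or non-parametric within-group comparison is calculated, as appropriate", and sets one threshold: "For all within-group comparisons, the significance level is set at *p* ≤ 0.05". It mentions no multiplicity control.
- Protocol, section 4.3, gives a sensitivity analysis for 50 patients: d = 0.4 at power 0.8 and d = 0.52 at power 0.95.
- Only question 3 (10mWT, TUG, TUG+DT and stairs) is called exploratory. Question 1 is the main question.

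**The concern.** Taken together, these sections give the main question 12 chances of a significant result, each at the full 5% level, and a hypothesis that a single subtest can satisfy. Even if masks have no effect, a positive answer is then more likely than the nominal level suggests.

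Section 7.3 wants to learn which aspects of gait adaptability are most likely to be affected and to derive recommendations. The risk-benefit section foresees changes to care and therapy if an influence is shown. A falsely significant subtest would feed directly into both. Section 2.6 plans a Registered Report, in which the method approved at Stage 1 governs publication, so the rule is best settled before that approval.

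**Working it through.** **Inputs**
- Subtests: 6. Difficulty levels: 2 (section 2.2.1). Primary comparisons: 6 × 2 = 12.
- Significance level: 0.05 per comparison (section 2.5).
- Patients: 50, each tested with and without a mask (sections 2.1 and 4.3).
- Sidedness: not stated.
- Correlation between the 12 mask-minus-no-mask differences: not given, so varied from 0 to 0.9 as an assumption.

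**Step 1. Reproduce the plan's own figure.** Power of a paired t-test from the noncentral t distribution with 49 degrees of freedom and noncentrality d × √50:

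| Test assumed | d at power 0.80 | d at power 0.95 |
| --- | --- | --- |
| One two-sided paired t-test at 0.05 | 0.404 | 0.520 |
| One one-sided paired t-test at 0.05 | 0.357 | 0.472 |
| Two independent groups of 25, two-sided 0.05 | 0.81 | 1.04 |
| Stated in section 4.3 | 0.4 | 0.52 |

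Of these, only the first row matches. Section 4.3 therefore describes a single two-sided paired test at the full 0.05, and two-sided tests are used below.

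**Step 2. Expected false positives with no mask effect.** 12 × 0.05 = 0.6 significant results, of which 12 × 0.025 = 0.3 point in the worse direction. These averages do not depend on the correlation.

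**Step 3. Chance of at least one false positive, independent comparisons.**
- Worse direction only: 1 − 0.975^12 = 0.262.
- Either direction: 1 − 0.95^12 = 0.460.

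**Step 4. Correlated comparisons.** Simulation of 12 equally correlated paired t-tests, 50 patients, 40,000 runs per row, no true effect:

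| Assumed correlation | Worse direction | Either direction |
| --- | --- | --- |
| 0 | 26% | 46% |
| 0.3 | 21% | 40% |
| 0.5 | 16% | 32% |
| 0.7 | 12% | 24% |
| 0.8 | 9% | 19% |
| 0.9 | 7% | 14% |

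Hypothesis 1 predicts worse performance, so the middle column is the relevant one. If the tests were instead one-sided at 0.05, the chance would be 46% at correlation 0, 27% at 0.5, 20% at 0.7 and 12% at 0.9.

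**Step 5. Effect of control on power.** Holm's strictest step is 0.05/12 = 0.00417. At that level, with 50 patients and a two-sided paired t-test:

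| | One test at 0.05 | At 0.05/12 |
| --- | --- | --- |
| d for power 0.80 | 0.404 | 0.547 |
| d for power 0.95 | 0.520 | 0.666 |
| Power at d = 0.40 | 79% | 44% |
| Power at d = 0.52 | 95% | 74% |

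At that level, 80% power at d = 0.40 would need about 90 patients. Holm's later steps are less strict (0.05/11, 0.05/10 and so on), so these are worst-case figures for a single subtest.

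**The case against.** **The protocol never says that p-values are unadjusted.** This is true. Adjusted p-values compared with 0.05 would satisfy the sentence in section 2.5, and a statistical analysis plan, which is not shown, could specify them. A reader might infer that the protocol rules out adjustment, but its text does not say so. What stands against the objection is section 4.3: its figures are those of one test at the full 0.05. A correction added elsewhere would leave that section wrong, so the point is more than a detail deferred to another document.

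**No sentence says that one significant result out of 12 confirms Hypothesis 1.** This is also true. Section 1.3 states where an effect may appear, and section 7.3 lists whether masks matter and which aspects are affected as separate items. One could therefore read the plan subtest by subtest, with no overall verdict. The any-one rule is an inference from sections 1.3, 2.2.1 and 2.5, though the natural one, since the hypothesis explicitly allows for significance on single subtests. Under the subtest-by-subtest reading, the list of affected subtests would still carry uncontrolled false positives.

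**46% overstates the problem.** A reader might take it as the error rate of Hypothesis 1. It is not: it counts improvements with a mask, which cannot support the hypothesis, and it assumes independence, although all scores come from the same patients at one fixed walking speed.

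**The study is small and the topic new.** That justifies modest claims and a feasibility-based sample size. It does not make question 1 exploratory, because the protocol reserves that label for question 3.

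**Conclusion.** The point holds. As written, the protocol sets 12 primary comparisons at 0.05 each, with no stated multiplicity control and a hypothesis that one significantly worse subtest would naturally support. With no true mask effect, the chance of such support is 26% under independence, falling to 16%, 12% and 7% at correlations of 0.5, 0.7 and 0.9. It exceeds 5% in every case examined. The excess is large at low to moderate correlation and small only when the outcomes are very highly correlated.

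The result rests on two-sided tests (inferred from section 4.3), on equal correlation among the 12 differences, and on all 50 patients contributing to each comparison. Section 2.2.1 has both levels done only where patients can manage them, so some comparisons may have fewer pairs. That leaves the count of 12 unchanged but would lower power below the figures shown.

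**What to change.** - **Section 2.5:** state that, for question 1, the family-wise error is controlled at 5% over the 12 subtest-by-level comparisons with Holm's procedure. State also that Hypothesis 1, and any subtest named as affected, rests on a Holm-adjusted p ≤ 0.05 in the worse direction. State that the tests are two-sided.
- **Section 1.3:** align the wording of Hypothesis 1 with that rule. Keep the question 3 tests labelled exploratory, and say that they are unadjusted.
- **Section 4.3:** say that d = 0.40 and 0.52 apply to one test at 0.05. Add that at Holm's strictest step, with 50 patients, they become about 0.55 and 0.67, and that power at d = 0.40 falls from 79% to 44%.

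A single global test on a mean CGait score, placed before the subtests, is not recommended as things stand. The score would first have to be defined across both levels and for patients who do not complete one of them, and its place in the confirmation rule made clear. It could also miss an effect confined to one or two subtests.

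The cost is a few sentences in three sections, best made before Stage 1 review, and lower power for each subtest. Holm controls the error under any correlation and needs no extra data or patients.

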## Test plan

### 2.1. study procedure

The project will investigate the extent to which wearing a facemask affects gait adaptability (CGait) and mobility (clinical parameters) in people with neurological disease.

For this purpose, 50 patients who are undergoing rehabilitation at the neurological rehabilitation center "Godeshöhe" (NRZ) will be asked whether they would like to participate in this study with a measurement point. They will be informed verbally and in written form about the study project. If they wish to participate, they must give their written consent to participation and data processing.

Afterwards, some socio-demographic (age, gender, years of education, height, shoe size, weight, BMI, spectacle wearer, type of visual impairment), and clinical (diagnosis, year of diagnosis, disease severity, fall events in the last 12 months, subjective fear of falling, medication, if applicable, pacemaker settings in people with Parkinson's disease) data are recorded. These are collected in order to be able to describe the sample decisively.

As primary endpoint, the CGait walking test will be completed once with and once without mask by each participant. The order "mask/no mask" will be randomized per participant. Among all participants, the order "mask/no mask" will be equally frequent as the order "no mask/mask". The CGait test is a standard test that is integrated into the diagnostic program of the C-Mill by Motek VR treadmill (DIH GmbH, Cologne, GER). It lasts 20 minutes and includes a series of tasks to test gait adaptability, including crossing obstacles (see Section 2.2.1). In addition, standard motor diagnostic tests (10mWT, TUG, TUG+DT and stair test) are collected. Figure 1 illustrates the planned measurement procedure. Chapter 2.2. gives an overview of the planned data collection

[figure not shown]

Figure 1: Schematic representation of the study process

### 2.2 Assessments

The data to be collected will be obtained by interview (sociodemographic and clinical data and subjective assessments) and simple clinical examination (motor gait and balance tests). Table 1 summarizes the assessments planned for the study. Most of the data to be collected in the project will be collected in the usual routine. Therefore, the additional burden for the subjects is low (85 min.).

The sociodemographic and clinical data can largely be taken from the digital file. However, they are verified in personal interviews with the patients and the treating physicians (questioning).

The recording of past fall events and fall-associated self-efficacy is carried out by means of standardized questionnaires. The self-evaluation of the test persons is carried out with self-developed questionnaires.

During motor testing, various facets of mobility are recorded using standardized assessments for neurological rehabilitation. The testing is performed by experienced physiotherapists and/or sports scientists who have been familiar with the testing for many years. The assessments cannot be blinded due to staff resources.

Table 1: Planned assessments

| **Tests** | **Form of collection** | **Duration** | **Routine** | **T0** |
| --- | --- | --- | --- | --- |
| Sociodemographic data (total duration approx. 7 min.) | | | | |
| Age in years | File/ Questioning | < 1min. | x | x |
| Gender | File/ Questioning | < 1min. | x | x |
| Training years | File/ Questioning | < 1min. | x | x |
| Weight in Kg | File/ Questioning | < 1min. | x | x |
| Body height in cm | File/ Questioning | < 1min. | x | x |
| Body Measure Index, BMI | Is calculated from height and weight (formula of WHO )^[[1]](#footnote-1)^ |  |  |  |
| Shoe size | Survey | < 1min. |  | x |
| Spectacle wearer | Survey | < 1min. |  | x |
| Type of visual impairment | Survey | < 1min. |  | x |
| Clinical data (total duration approx. 13 min.) | | | | |
| Diagnosis incl. progression form/ type | File/ Questioning | < 1min. | x | x |
| Time since diagnosis (in months) | File/ Questioning | < 1min. | x | x |
| Severity of illness (Expanded Disability Status Scale, EDSS Kurtzke, *Neurol,* 1983; Hoehn & Yahr Scale.  Hoehn & Yahr, Neurol, 1967) | File/survey for motor. Testing | 5 min. | x | x |
| Fall events in the last 12 months | Survey | < 1min. |  | x |
| Fall-associated self-efficacy (Activities-Specific Balance Confidence Scale, ABC *Schott, Z Gerontol Geriat, 2008*). | Interviews | 5 min | x | x |
| Motor data (total duration 45 min., 2x each) | | | | |
| Gait adaptability (CGait, Timmermanns et al, *Phys Ther*, 2019). | Motor Test | 20 min | x | x |
| 10m walking distance (10mWT; ) | Motor Test | 5 min. | x | x |
| Functional mobility and balance (Timed Up and Go Test, TUG Mathias et al, *Arch Phys Med Rehabil*, 1986). | Motor Test | 5 min. |  | x |
| Walking with dual task (TUG with dual task, TUG+DT Hofheinz et al., *HeilberufeScience*, 2011). | Motor Test | 10 min |  | x |
| Ascending and descending stairs (acending/ decending stair test Nightingale, *J Rehabil Res Dev*, 2014). | Motor Test | 5 min. |  | x |
| Respondent interview (total duration 20 min.) | | | | |
| Subjective assessment of subjects on performance with/without mask | Survey | 15 min |  | x |
| Subjective assessment of the C-Mill by test persons | Survey | 5 min. |  | x |

*Total duration*: 150 min. of which exclusively study-related testing approx. 85 min.

*The following applies to the assessments*: If individual limitations arise due to the clinical picture or if the patients need a break for any reason, which they do not need to specify, or do not wish to continue the test/questionnaire, the test/questionnaire will be interrupted or terminated.

